# Ergothioneine supplementation in people with metabolic syndrome (ErgMS): protocol for a randomised, double-blind, placebo-controlled pilot study

**DOI:** 10.1186/s40814-021-00929-6

**Published:** 2021-10-29

**Keywords:** Ergothioneine, Metabolic syndrome, Supplementation, Metabolome, Oxidative stress, Inflammation, ALT

## Abstract

**Background:**

Ergothioneine is a naturally occurring metabolite of histidine found in many foods and in high amounts in mushrooms. In vivo, ergothioneine acts as an antioxidant and is widely distributed in most mammalian tissues. While ergothioneine is sold as a dietary supplement for its antioxidant and anti-inflammatory properties, to date there are no published intervention trials examining its health benefits in humans. The aim of this work was to develop a study protocol for a pilot interventional trial that will establish the primary and secondary outcomes, and the power required, for a definitive randomised controlled trial to test the hypothesis that ergothioneine supplementation is beneficial for people with metabolic syndrome.

**Methods:**

We have designed the ErgMS study as a single-centre, randomised, double-blind, placebo-controlled, 3-arm parallel, pilot intervention trial, which aims to supplement participants with either placebo, 5 or 30 mg/day ergothioneine for 12 weeks. Measurements of metabolic syndrome risk factors, serum markers of oxidative stress (lipid peroxidation), inflammation, blood platelet function and liver function will take place at baseline, and after 6 weeks and 12 weeks of supplementation. In addition, we will examine if there are any changes in the serum metabolome in response to ergothioneine supplementation. Linear regression and two-way ANOVA will be utilised to analyse the association between ergothioneine and measured variables.

**Discussion:**

The ErgMS study will be the first study to address the question does ergothioneine supplementation have health benefits for people with metabolic syndrome. Study results will provide preliminary data as to which dose may improve inflammatory markers in adults with metabolic syndrome and will inform dose and primary outcome selection for a definitive randomised controlled trial.

**Trial registration:**

ISRCTN, ISRCTN25890011 Registered February 10^th^, 2021

**Supplementary Information:**

The online version contains supplementary material available at 10.1186/s40814-021-00929-6.

## Introduction

### Background and rationale

Ergothioneine is a naturally occurring metabolite of histidine found in many different foods [1, 2]. Synthesized by bacteria and fungi, ergothioneine is found in particularly high amounts in mushrooms. An amino acid betaine (2-mercapto-histidine trimethylbetaine), ergothioneine has robust cytoprotective properties with roles as a metal chelator as well as an antioxidant, scavenging hydroxyls and other free radicals [3]. As recently reviewed in detail, a growing body of evidence implicates ergothioneine as an important nutrient for healthy ageing and the prevention of a variety of inflammatory diseases, including cardiometabolic diseases [4, 5]. Notably, a long-term prospective cohort study (*n* = 3236 participants with median follow-up of 21.4 years) found that higher plasma levels of ergothioneine were associated with significantly lower risk of coronary disease, cardiovascular mortality and overall mortality (hazard ratios per 1 SD increment of ergothioneine 0.85, 0.79 and 0.86 respectively), as well as a more ‘health-conscious food pattern’ [6].

In vivo, ergothioneine is transported across cell membranes by the solute carrier family 22 member’s 4 and 15 (SLC22A4, SLC22A15) [7–10]. Although many SLC22 family members are non-selective transporters, evidence suggests that SLC22A4 is highly specific for ergothioneine [9, 10]. Widely expressed in most tissues, SLC22A4 is particularly highly expressed in the small intestine where it functions to take ergothioneine up from the diet, and in the kidney where it is presumed to function in renal reabsorption [5]. A pharmacokinetic study of healthy humans taking encapsulated ergothioneine (5 and 25 mg/day) found that ergothioneine is rapidly absorbed and largely retained by the body, with large increases in plasma ergothioneine levels and only minimal increases (< 4%) in urinary excretion observed [11]. Avid absorption and retention of ergothioneine has also been observed in a study in mice, which showed ergothioneine accumulated in liver as well as whole blood [12]. Genetic knockout of SLC22A4 in both mice and zebrafish results in almost complete deficiency of ergothioneine in tissues and increased susceptibility to oxidative stress and inflammation, although organisms remain viable [8, 13].

The existence of a physiologic transporter for ergothioneine along with its antioxidant and cytoprotective roles has raised the question of whether or not ergothioneine should be designated a vitamin [14]. Notably, Ames (2018) has proposed that ergothioneine belongs to a class of ‘longevity vitamins,’ namely dietary compounds not necessarily required for early survival, but that support health and that without which organisms experience accelerated ageing [15]. Supporting this idea are data showing that knockout of SLC22A4 in *Caenorhabditis elegans* increased oxidative damage and reduced lifespan [16], as well as the aforementioned association of high plasma ergothioneine levels with reduced mortality in humans [6]. In a similar vein, Borodina and colleagues (2020) suggest that ergothioneine can be considered a nutraceutical, i.e. a nutrient that when taken at higher amounts than typically found in the diet provides health benefits [4]. Indeed, ergothioneine is already sold as a dietary supplement. The European Food Safety Authority (EFSA) published their safety assessment and scientific opinion for ergothioneine in 2016, determining the no observed adverse effect level (NOAEL) of ergothioneine as 800 mg/kg body weight per day and concluding a supplemental dose of 30 mg/day well within safety margins [17]. Subsequently, the US Food and Drug Administration in 2018 approved ergothioneine as generally recognised (GRAS notice 734) [18].

These regulatory approvals facilitate the needed intervention trials to investigate the potential health benefits of ergothioneine supplementation in humans. In spite of the evidence from pre-clinical models and studies in humans associating low/high blood levels of ergothioneine with disease/health, evidence from randomised controlled trials (RCTs) is lacking. To date, only one study, focused on uptake and pharmacokinetics, has been published examining ergothioneine supplementation in humans [11]. In this placebo-controlled intervention study, 45 participants received either placebo, 5 or 25 mg ergothioneine/day for 7 days and were followed up for an additional 4 weeks; there were no reported adverse effects. While no significant changes in oxidative or inflammatory markers were observed, participants were healthy, the supplementation period was short and the study was likely underpowered to examine these. Currently, a larger and longer-term study is ongoing in Singapore examining the efficacy of ergothioneine (25 mg given 3 times a week for 52 weeks) to delay or reverse cognitive impairment in elderly individuals with mild cognitive impairment [19]. However, a planned study in the USA that aimed to examine the effects of ergothioneine on cognition, mood and sleep in healthy adults has been terminated in the context of COVID [20].

Metabolic syndrome is a cluster of risk factors associated with type 2 diabetes and cardiovascular and atherothrombotic diseases [21]. Oxidative stress plays an important role in the pathogenesis of metabolic syndrome and its downstream morbidities [22]. Given the lack of data in humans, in order to address the hypothesis that ergothioneine supplementation may reduce markers of systemic and cellular oxidative stress and inflammation in people with metabolic syndrome, a pilot study is necessary to establish the primary and secondary outcomes and power required for a definitive RCT. The ErgMS study aims to establish these and will be the first study to investigate potential health benefits of ergothioneine in people with metabolic syndrome.

### Study aims

The overall aims of this trial are to determine the feasibility of supplementing people with metabolic syndrome with ergothioneine for 12 weeks, and to establish primary and secondary outcomes and the power required for a definitive RCT to establish the benefit of ergothioneine on markers of oxidative stress, liver damage, inflammation and metabolic syndrome risk factors among people with metabolic syndrome.

### Study objectives

To assess feasibility of recruiting and supplementing people with metabolic syndrome with ergothioneine for 12 weeks.To investigate if any changes in serum markers of oxidative stress (lipid peroxidation), inflammation and liver function can be observed in response to ergothioneine supplementation.To examine if any changes in oxidative and inflammatory stress in blood immune cells can be observed in response to ergothioneine supplementation.To assess if there are any changes in metabolic syndrome risk factors or in the serum metabolome in response to ergothioneine supplementation.To use the data to determine dose of ergothioneine and participant numbers needed to inform a primary outcome for a definitive randomised controlled trial.

### Study design

The ErgMS study has been designed as a single-centre randomised, double-blind, placebo-controlled, 3-arm parallel, pilot interventional trial.

Consenting participants with metabolic syndrome risk factors will be randomised in a double-blind fashion to one of three parallel arms to receive either placebo (0 mg ergothioneine), 5 mg ergothioneine or 30 mg ergothioneine for consumption as daily capsules (one per day) for 12 weeks (Fig. 1). The dose of 30 mg is well within the NOAEL of 800 mg/kg body weight set by EFSA [17]. Participants will give blood samples and undergo anthropometric measurements at three timepoints, baseline, 6 weeks and 12 weeks (Fig. 1). The ErgMS protocol was designed following the Standard Protocol Items: Recommendations for Interventional Trials (SPIRIT) guidance [23] and has been prospectively registered with the ISCRCTN registry, reference: ISRCTN25890011 10.1186/ISRCTN25890011.

**Fig. 1 Fig1:**
[figure not shown]
ErgMS Study design. *BMI* body mass index, *BP* blood pressure, *FFQ* food frequency questionnaire, *TAG* triacylglyceride, *HDL*-*C* high-density lipoprotein-cholesterol

## Methods

### Study setting

The study will be conducted at the School of Food Science and Nutrition at the University of Leeds, in Leeds, West Yorkshire, the UK.

### Eligibility criteria

#### Inclusion criteria

Consenting participants must be 18–70 years old and have risk of metabolic syndrome, defined by presenting with at least two of the six following criteria; with cut-offs based on the 2009 consensus definition of metabolic syndrome and population-specific thresholds for defining excess central adiposity [21]:BMI ≥ 25 kg/m^2^;Abdominal obesity: high waist circumference (Asian/Asian British—men ≥ 90 cm; women ≥ 80 cm; White and all other ethnic groups—men ≥ 94 cm, women ≥ 80 cm);Fasting glucose ≥ 100 mg/dl (5.6 mmol/l) or treatment for elevated blood glucose;Blood pressure ≥ 130/85 mmHg or treatment for elevated blood pressure;Triacylglycerides (TAG) ≥ 150 mg/dl (1.7 mmol/l) or treatment for elevated TAG;Cholesterol-high density lipoprotein (HDL-C) < 40 mg/dl (1.0 mmol/l) for male or < 50 mg/dl (1.3 mmol/l) for female or treatment for low HDL-C.

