An additional potential implication from the ErgMS design is that while the exclusion criteria reflect our objective of focusing on metabolic syndrome and excluding other inflammatory conditions, the large number of exclusion criteria may result in a longer recruitment period. Nonetheless, the ErgMS study will be the first study to address the question does ergothioneine supplementation have health benefits for people with metabolic syndrome. Study results will provide novel, preliminary data as to which dose may improve inflammatory markers in adults with metabolic syndrome, and inform dose and primary outcome selection for a definitive RCT.

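### The entry rule admits adults with any two metabolic syndrome risk factors, but the title, aims and conclusions claim a population that has metabolic syndrome

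*Protocol article*

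**What the plan says.** **Who may enter.** Under Inclusion criteria, participants aged 18–70 must "have risk of metabolic syndrome, defined by presenting with at least two of the six following criteria". The six are BMI, waist circumference, fasting glucose, blood pressure, triacylglycerides (TAG) and HDL cholesterol (HDL-C). The last four can also be met by being on treatment. BMI of at least 25 kg/m² is one item and "Abdominal obesity: high waist circumference" is another. The section ties the thresholds to a published definition ("with cut-offs based on the 2009 consensus definition of metabolic syndrome") but does not attribute the two-of-six count to it. Study design uses similarly cautious wording: "Consenting participants with metabolic syndrome risk factors will be randomised in a double-blind fashion".

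**Whom the trial says it is about.** Study aims sets out to "determine the feasibility of supplementing people with metabolic syndrome with ergothioneine for 12 weeks" and to prepare a definitive trial of benefit on "markers of oxidative stress, liver damage, inflammation and metabolic syndrome risk factors among people with metabolic syndrome". The title, the abstract, the first study objective and the Monitoring section name the same population. The Discussion closes with: "Study results will provide novel, preliminary data as to which dose may improve inflammatory markers in adults with metabolic syndrome".

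**What the data are for.** Recruitment and completion are primary feasibility outcomes. The last study objective is to use the data to settle the dose and the number of participants for the definitive trial. Secondary exploratory outcomes puts MDA forward as the likely outcome for powering it.

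**The concern.** Being at risk of a condition is not the same as having it, and the article uses both descriptions for one group of participants. Its background section describes the syndrome this way: "Metabolic syndrome is a cluster of risk factors associated with type 2 diabetes and cardiovascular and atherothrombotic diseases". Under the entry rule, two measures of body size are enough, with nothing abnormal in glucose, blood pressure or lipids.

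This matters because the pilot exists to hand numbers to a later trial in a named population. Two kinds of result are affected:

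- **Feasibility.** The number recruited answers how readily adults with two or more risk factors can be found. Read as the recruitment rate for people who have the syndrome, it would be optimistic to the extent that the full definition is narrower than the entry rule.
- **Planning values.** Means, SDs and effects, for MDA in particular, would come from the broader group but be labelled as belonging to the narrower one.

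**Working it through.** The plan gives no figure to reproduce here. The check has two parts: a comparison of the passages, and a count of what the entry rule allows.

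**1. Passages side by side**

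| Section | Population described |
|---|---|
| Inclusion criteria | at risk of the syndrome; any two of six criteria |
| Study design | having risk factors for the syndrome |
| Title; abstract | people or adults with the syndrome |
| Study aims; first study objective | people with the syndrome |
| Monitoring | adults with the syndrome |
| Discussion | people or adults with the syndrome |

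The two places that say who is actually randomised use the weaker description. The places that say what the trial is for, and what it will show, use the stronger one. The Discussion also says that the exclusion criteria reflect a focus on metabolic syndrome, so the stronger label is not an isolated slip.

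**2. What the entry rule allows**

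Input: six criteria, each met or not met, with at least two required (Inclusion criteria).

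- All combinations: 2^6 = 64.
- Not eligible: 1 with no criterion met + 6 with exactly one = 7.
- Eligible: 64 − 7 = 57, of which 6 × 5 / 2 = 15 have exactly two criteria.
- Eligible with glucose, blood pressure, TAG and HDL-C all unmet: both remaining items must be met, so there is exactly 1, BMI plus waist.

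Nothing in the Exclusion criteria removes that combination.

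**3. What tighter counting would do**

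- BMI and waist merged into one adiposity item, with two distinct items still required: 57 − 1 = 56 combinations remain.
- BMI dropped, with two of the other five required: 2 × (2^5 − 1 − 5) = 2 × 26 = 52 combinations remain.

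These are counts of combinations, not of people. One combination in 57 does not mean that 1 in 57 participants will have it; the true share could be far larger or smaller. The article gives no prevalence for any criterion.

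**The case against.** The strongest reply is that the entry rule is openly stated. Inclusion criteria and Study design agree with each other, and only the framing sections use the looser label. This is a pilot with feasibility as its primary outcome, and biomarker effects are exploratory. All six measurements are taken at baseline, so participants can be described later without a design change. Detailed baseline tables are often left to a fuller document that is not shown here. One recruitment route is people with metabolic syndrome from an earlier study, although broad advertising is used as well.

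Much of this stands. It shows that the problem lies in how the population is named, and that no missing table should be held against the article. It does not remove the conflict: the rule and the claims are both printed, and they name different populations.

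A reader might infer three stronger points, which the documents do not support:

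- **That adiposity-only participants will be enrolled in number.** They can be enrolled; how many will be is unknown.
- **That the definitive trial's sample size would be inflated by a known factor.** If a share f had no response and the SD were unchanged, the factor would be 1/(1 − f)². An assumed f of 20% to 40% gives 1/0.8² = 1.56 to 1/0.6² = 2.78. But nothing in the article anchors f. Normal glucose, blood pressure and lipids do not imply that MDA cannot respond. And if the definitive trial kept the same entry rule, the pilot's estimate would be the right planning value.
- **That merging BMI with waist would cure the mismatch.** It removes one combination of 57 and leaves a population defined by two risk factors. It also works against recruitment, which the Discussion already expects the many exclusion criteria to prolong.

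**Conclusion.** The concern holds as a contradiction between the entry rule and the population named in the title, aims, objectives, monitoring rationale and conclusions. As written, the recruitment result and the planning values would be attributed to people who have metabolic syndrome, whereas they would describe adults with at least two risk factors. Some of those adults may have excess weight as their only feature.

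The conclusion rests on the text alone. It does not depend on how many criteria the cited 2009 definition requires, which the article does not give, or on any assumption about who responds to ergothioneine. The size of the effect cannot be stated, because neither the share of participants below the full definition nor the direction of any shift in the MDA mean or SD can be derived from the documents. The point bears on what the pilot can claim and pass on; it does not invalidate the randomised comparison between arms.

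**What to change.** Reconcile the passages:

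1. Restate the population in the title, aims, objectives and conclusions as *adults with at least two metabolic syndrome risk factors*, and bring the Monitoring section into line.
2. Report by arm the number and type of criteria met, marking those met through treatment rather than by a measured value.
3. Show recruitment, and the MDA mean and SD, for all participants and again for those who meet the full cited definition. State that definition in the report. A definitive trial with narrower entry then has the figures that it needs.

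The cost is a wording change and a little extra tabulation. The six measurements are already scheduled at baseline; the one item to confirm is that qualification by treatment is recorded.

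Counting BMI and waist as a single criterion is optional. It would require an amendment and could slow recruitment, and item 1 would still be needed.

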#### Exclusion criteria

People who are unwilling or unable to provide informed consent;Women who are pregnant or lactating;Smokers or people who consume ≥ 28 units of alcohol per week (28 units = ~ 10 medium glasses of wine (175 ml) or ~ 10 pints of beer/cider);People following lifestyle change advice, e.g. newly implemented diet or exercise regime (≥ 150 min/week moderate aerobic exercise or ≥ 75 min/week vigorous aerobic exercise) aimed at weight loss;People who have regularly (≥ 3 times/week) taken dietary/antioxidant supplements within the last 4 months;People taking prescription anti-inflammatory medicines (occasional aspirin, paracetamol, ibuprofen use acceptable);Antibiotic treatment within last month or 3 courses within the last 6 months;Diagnosis of cancer or end of cancer treatment within 2 years;Diagnosis of heart, kidney or gastrointestinal diseases or people who have had surgical treatment for obesity;People diagnosed with a blood borne disease (HepB, HIV etc.);Participation in other clinical trials that may influence outcomes;In the context of COVID-19 safe procedures, people who cannot wear a face mask during the visit

### Consent

Electronic copies of the participant information leaflet and consent form will be sent to any potential participants when they show interest in the ErgMS study and provide their email address requesting more information. Preliminary screening will be done online and an online consent form must be signed before the screening questionnaire will be released. At the baseline visit, informed consent will be confirmed with electronic written consent taken prospectively from the participants by the site study team in advance of collecting any data. The consent form will ask volunteers to confirm their understanding that the samples and data collected will be used to support other research in the future, and may be shared anonymously with other researchers. The form will also give potential participants the option to agree to be contacted for future studies. Only adults (> 18 years old) who have the capacity to provide consent to participate will be included. The ErgMS study will be conducted according to the principles of Good Clinical Practice, and to the ethical principles that have their origin in the Declaration of Helsinki.

### Interventions

Consenting participants will be randomised in a double-blind fashion to one of three intervention groups that will receive either placebo (0 mg ergothioneine), 5 mg ergothioneine or 30 mg ergothioneine for consumption as daily capsules (one per day) for 12 weeks (Fig. 1). Both placebo and ergothioneine supplement capsules will be manufactured by Tetrahedron (Paris, France). The placebo capsules will have the same shape, colour, weight and packaging as the ergothioneine capsules. Participants can withdraw from the study at any time if they want to withdraw without reasons by contacting the researcher. Data already collected from any withdrawals will be kept in the dataset and used in intention-to-treat analysis.

To promote adherence, participants will be sent periodic reminder/enquiry texts before each visit and will be informed of their clinical parameters at each visit and the final results after the trial data has been analysed and unblinded. Supplementation compliance will be measured both by capsule counting (participants will be asked to return package and untaken supplements at 6 weeks and 12 weeks) and the measurement of ergothioneine in plasma by high-performance liquid chromatography (HPLC) at baseline, 6 weeks and 12 weeks.

Related to the exclusion criteria, participants will be asked not to start taking dietary/antioxidant supplements, implement a new diet/fitness regime or take prescription anti-inflammatory medicines (occasional aspirin, paracetamol, ibuprofen use acceptable) for the duration of the trial.

